# OCOSO2: study protocol for a single-blinded, multicentre, randomised controlled trial assessing a central venous oxygen saturation-based goal-directed therapy to reduce postoperative complications in high-risk patients after elective major surgery

**DOI:** 10.1186/s13063-023-07689-z

**Published:** 2023-10-11

## Abstract

**Background:**

Fluid loading-based goal-directed therapy is a cornerstone of anaesthesia management in major surgery. Its widespread application has contributed to a significant improvement in perioperative morbidity and mortality. In theory, only hypovolemic patients should receive fluid therapy. However, to achieve such a diagnosis, a surrogate marker of cardiac output adequacy must be used. Current methods of fluid loading-based goal-directed therapy do not assess cardiac output adequacy. Nowadays, new devices make it possible to continuously monitor central venous oxygen saturation (ScvO_2_) and therefore, to assess the adequacy of perioperative cardiac output during surgery. In major surgery, ScvO_2_-based goal-directed therapy can be used to enhance fluid therapy and improve patient outcomes.

**Methods:**

We designed a prospective, randomised, single-blinded, multicentre controlled superiority study with a 1:1 allocation ratio. Patients to be included will be high-risk major surgery patients (> 50 years old, ASA score > 2, major intra-abdominal or intra-thoracic surgery > 90 min). Patients in the control group will undergo standard fluid loading-based goal-directed therapy, as recommended by the guidelines. Patients in the intervention group will have ScvO_2_-based goal-directed therapy and receive fluid loading only if fluid responsiveness and cardiac output inadequacy are present. The primary outcome will be the Comprehensive Complication Index on day five postoperatively.

**Discussion:**

This study is the first to address the issue of cardiac output adequacy in goal-directed therapy. Our hypothesis is that cardiac output optimisation during major surgery achieved by continuous monitoring of the ScvO_2_ to guide fluid therapy will result in a reduction of postoperative complications as compared with current goal-directed fluid therapy practices.

**Trial registration:**

ClinicalTrials.gov. NCT03828565. Registered on February 4, 2019.

**Supplementary Information:**

The online version contains supplementary material available at 10.1186/s13063-023-07689-z.

## Introduction

### Background and rationale

Fluid loading is a cornerstone of anaesthesia management in major surgery. Indeed, both fluid overload and hypovolaemia are deleterious for surgical patients [1, 2].

Several studies have assessed fluid loading based on clinical variables (arterial pressure, urine output, heart rate) and against goal-directed variables (cardiac output, stroke volume). These studies found a reduction in postoperative morbidity and length of hospital stay in goal-directed fluid therapy patients, including in long-term follow-up [3–6].

Since 2012, experts in the French Society of Anaesthesia and Intensive Care Medicine have recommended using goal-directed therapy for fluid loading in high-risk surgery patients [7]. These guidelines require the assessment of dynamic fluid responsiveness before administering fluid. If the patient is not a fluid responder, fluid loading is not administered. This strategy makes it possible to stop fluid loading as soon as it becomes deleterious.

However, it is not known whether fluid responsiveness alone is sufficient to determine the need for fluid loading. Indeed, with regard to the Frank-Starling law, fluid responsiveness is a physiological status, which means that there is no need to provide fluid in all responders [8]. Hypovolaemia is defined as a decrease in venous return, which is significant enough to cause an inadequacy of cardiac output. In theory, only hypovolemic patients should receive fluid loading. To achieve this endpoint, a surrogate marker of cardiac output adequacy should be used, such as serum lactate concentration or central venous oxygen saturation (ScvO_2_).

Serum lactate concentration is a late marker of cardiac output adequacy. In addition, it is not sufficiently accurate to detect slight changes in cardiac output. In contrast, ScvO_2_ is an excellent surrogate for detecting cardiac output variations. Today, new devices make it possible to monitor ScvO_2_ continuously and therefore to assess the adequacy of perioperative cardiac output. This facility could be used to enhance fluid therapy during major surgery and improve patients’ outcomes.

### Objectives

Our hypothesis is that using the continuous monitoring of ScvO_2_ to guide fluid therapy during major surgery will result in better cardiac output optimisation with a reduction in postoperative complications as compared with current goal-directed fluid therapy practices.

### Trial design

This study will be a prospective, randomised, single-blinded, multicentre controlled superiority study with a 1:1 allocation ratio.

## Methods

### Study setting

Three French hospitals in which major surgery is performed: Hôpital Nord (Assistance Publique Hôpitaux Universitaires de Marseille, Aix Marseille Université, Marseille France), Institut Paoli Calmette (Marseille, France), Hôpital Caremeau (Centre Hospitalier Universitaire de Nîmes, Nîmes, France).

### Eligibility criteria

Adult patients over 50 years of age with an American Society of Anesthesiologists (ASA) score of between 2 and 4 who are scheduled for elective major surgery. Elective major surgery is defined as abdominal or thoracic surgery with a duration of at least 90 min and requiring the use of invasive blood pressure monitoring and a central venous line.

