### Sample size

A sample size calculation was made from published data [9, 11]. In order to show a 10% difference in CCI between groups on day five after surgery, with a 0.9 power and a 0.05 alpha risk, 100 patients were needed per group. Considering a potential 10% loss to follow-up, we included 220 patients (110 patients per group). We chose a 10% difference in CCI because this represents a clinically significant decrease in postoperative complications (one grade on the Clavien-Dindo classification).

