### Statistical methods

Statistical analysis will start only after the database has been validated (all queries answered, database coherence controlled). The statistical analysis will be blinded (no explicit identification of groups). The methodology and statistical analysis will be performed in accordance with the CONSORT statement [13]. The population analysis will be performed according to the intention-to-treat (ITT) principle. A secondary, per-protocol population analysis will be performed if needed. If present, missing data will be handled via multiple imputation by chained equations. Categorical variables will be reported as count (%) and continuous variables as mean (± standard deviation (SD)) or median (25th–75th quartile range). The presence of a normal distribution will be verified using the Kolmogorov-Smirnoff test. We will use the *t*-test to assess differences between parametric continuous variables, the Mann–Whitney test for non-parametric variables, the *χ*^2^ test for categorical variables and the Fisher exact test for 2 × 2 tables. No correction for multiple testing will be done. A two-sided *p* < 0.05 will be considered statistically significant. Stopping of the trial could also be based on interim data analysis if clearly one treatment is better than the other, but no interim analysis is planned.

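### The abstract requires ASA above 2 but the eligibility section admits ASA 2, so the article leaves its high-risk population undefined; the primary comparison also ignores ASA class

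*Protocol article*

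**What the plan says.** The Methods paragraph of the abstract states that those included will be "high-risk major surgery patients (> 50 years old, ASA score > 2, major intra-abdominal or intra-thoracic surgery > 90 min"). The ASA cut-off is part of the parenthesis that explains what high-risk means, and the title names high-risk patients as the target of the trial.

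The Eligibility criteria section takes patients over 50 with an "American Society of Anesthesiologists (ASA) score of between 2 and 4 who are scheduled for elective major surgery". It does not use the term high-risk. It adds the need for invasive pressure monitoring and a central venous line.

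The Protocol amendments section describes two changes. One concerns heart arrhythmia as an exclusion. The other concerns fluid loading at a norepinephrine threshold.

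ASA score is on the list of demographics in the section on data collection, management and analysis. For comparing groups, the Statistical methods section names the t-test, the Mann–Whitney test, the chi-squared test and the Fisher exact test. None of these uses a baseline covariate.

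**The concern.** ASA class is a core inclusion rule and here also serves to label the population. If class 2 is eligible, the abstract describes a sicker population than the one studied, and a reader of the abstract alone would apply the result to the wrong patients. If class 2 is not eligible, the Eligibility criteria section is wrong on its main risk criterion. Either way, the final report could choose its description of the population after the data are in.

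The second part follows from the first. ASA class is meant to grade how ill a patient is before surgery, so it can be expected to predict complications. The wider the range of classes admitted, the more of the variation in CCI may come from ASA class rather than from treatment. The Allocation section stratifies randomisation by centre only, so the design does not balance ASA class, and the named tests do not account for it.

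**Working it through.** This is a comparison of texts. ASA is a whole-number scale, so each statement can be written as a set of classes.

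| Statement | Reading | Classes admitted |
|---|---|---|
| Abstract, Methods | strictly above 2 | 3 and above, no upper limit |
| Eligibility criteria | range includes both ends (ordinary reading) | 2, 3, 4 |
| Eligibility criteria | range excludes both ends | 3 only |

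1. **Inclusive reading.** Class 2 is eligible in the body and excluded by the abstract.
2. **Exclusive reading.** Class 4 qualifies in the abstract and is excluded in the body. The conflict moves to the other end of the scale.
3. **Mixed reading.** Dropping the lower end and keeping the upper would give classes 3 and 4, which comes closest to the abstract. Nothing in the wording signals such a reading, and the abstract would still lack the upper limit.
4. **Amendments.** Neither described change touches ASA, so the difference is not a trace of superseded text.
5. **Other sections.** No other section restates the ASA limits or settles them.

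Can the consequence for power be calculated? The Sample size section states "In order to show a 10% difference in CCI between groups on day five after surgery, with a 0.9 power and a 0.05 alpha risk", and that "100 patients were needed per group". It gives no standard deviation and no control mean, so the figure cannot be reproduced forwards. If 10% is taken to mean 10 CCI points, and the test is two-sided as the Statistical methods section says, the standard deviation can only be solved backwards:

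SD = 10 × √(100/2) / (1.960 + 1.282) ≈ 21.8.

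That value returns 100 per group by construction and says nothing about ASA. A power loss would further need the share of class 2 patients and the treatment effect in each class. The article gives neither, so no figure is offered.

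**The case against.** The strongest reply is that this is only loose wording in an abstract. The Eligibility criteria section is the operative text, and the sections on data access say that a separate full protocol exists. That is fair as regards trial conduct. A reader might infer that the three centres are enrolling different kinds of patient; the article does not support this, because nothing shows that any centre screens from the abstract. What stands is that the published account does not settle the criterion.

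A reader might also infer that admitting class 2 leaves the trial underpowered. The article does not support that either. It never says that the planned difference was meant for classes 3 and above; if it was planned for classes 2 to 4, it is already the average over that mix and nothing is lost. The spread of CCI might also shrink as lower-risk patients are added, which would offset part of any loss.

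ASA is not the only mark of risk here. Age over 50, major surgery and invasive monitoring are also required, so class 2 patients who meet them may fairly be called high-risk. The label need not be wrong; it needs one definition. The small difference in how the two statements bound the 90-minute duration matters only for an operation of exactly that length and carries no weight.

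On adjustment, it can be said that covariates are commonly left to an analysis plan, which is not shown here. If that plan already adjusts for ASA class, this part is met. The article does, however, name the tests, and all of them are unadjusted.

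**Conclusion.** The inconsistency is certain on the text. It concerns one whole class of a core inclusion rule, and the article offers nothing that resolves it. The conclusion is limited to this: the article does not settle whether ASA 2 patients are eligible, nor whether a result stated for high-risk patients extends to them. No sample-size figure changes, and no loss of power or enrolment error is shown.

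The recommendation to adjust is an improvement to the stated analysis, not the correction of an error; the unadjusted tests remain valid in a randomised comparison. It rests on the assumption that ASA class predicts CCI. The gain in precision depends on how strongly it does so, which the article does not say.

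**What to change.** 1. Check the ASA criterion in the ethics-approved protocol and bring the abstract and the Eligibility criteria section into line with it. Take the answer from that document, not from the classes that happened to be enrolled.
2. Describe the population by that criterion in the abstract and in the results, as ASA 2–4 if class 2 is eligible. If the term high-risk is kept, state what it means.
3. Make the primary day-5 CCI comparison adjusted for ASA class, for example by a linear model with treatment and ASA class, or by a rank test stratified by ASA class if a non-parametric method is used. Record this before the database is validated and the groups are identified.
4. Reporting the CCI effect by ASA class is optional and would be descriptive only.

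The cost is a text correction and one covariate that is already on the case report form. No new data and no change in sample size are needed.

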### Interventions

#### Control group

Patients in the control group will be treated with standard care. Fluid loading will be performed in accordance with French guidelines [7]. The cardiac output and/or the stroke volume will be continuously monitored with FloTrac technology (pulse contour analysis, Edwards Lifesciences, USA) or CardioQ technology (oesophageal Doppler monitoring, Deltex Medical Group, UK).

If a diminution in cardiac output, stroke volume and/or mean arterial pressure of at least 10% of the initial values is observed, a rapid (5 min) fluid loading of 250 mL of balanced crystalloid solution will be administered. If the stroke volume and/or cardiac output increase by at least 10%, additional fluid loading will be administered. When the stroke volume and/or cardiac output do not increase or increase by less than 10%, fluid loading will be stopped. If the patient is not fluid responsive with a mean arterial pressure below 10% of the value of his or her preoperative mean arterial pressure, a diluted norepinephrine (16 µg mL^−1^) infusion will be started (Fig. 1).

**Fig. 1 Fig1:**
[figure not shown]
Overview of the control group protocol. Abbreviations: SV, stroke volume; CO, cardiac output; MAP, mean arterial pressure

#### Intervention group

Patients in the intervention group will be treated via an algorithm based on continuous perioperative ScvO_2_ monitoring (PreSep, Edwards Lifesciences, USA).

If ScvO_2_ is above 70%, cardiac output will be defined as adequate. A diluted norepinephrine infusion will be used to maintain a mean arterial pressure within a 10% variation of the value of the preoperative mean arterial pressure, regardless of fluid responsiveness status.

If ScvO_2_ is above 70%, but the need for norepinephrine is above 0.5 µg kg^−1^ min^−1^ to reach the blood pressure targets, a fluid loading of 250 mL of crystalloids will be administered. Administration will be repeated every 15 min until the norepinephrine dosage is below 0.5 µg kg^−1^ min^−1^.

If ScvO_2_ is below 70%, cardiac output will be defined as inadequate. First, three out of the four determinants of ScvO_2_ will be assessed and corrected as needed (haemoglobin, arterial oxygen saturation and oxygen consumption through to the level of sedation). Then, fluid responsiveness will be assessed as described above. If the patient is fluid responsive, a fluid loading of 250 mL will be administered. If ScvO_2_ increases above 70%, fluid loading will be stopped. If not, the fluid loading will be administered as long as ScvO_2_ remains below 70%, with positive fluid responsiveness. If the patient is in the “grey zone” (when the fluid responsiveness assessment is not informative), the patient will be reassessed after 5 min (Fig. 2).

**Fig. 2 Fig2:**
[figure not shown]
Overview of the intervention group protocol. Abbreviations: ScvO2, central venous oxygen saturation; SaO2, arterial oxygen saturation; Hb, haemoglobin; BIS, bispectral index; MAP, mean arterial pressure; TTE, transthoracic echography; TEE, transoesophageal echography

### Outcomes

The primary outcome will be the Comprehensive Complication Index (CCI) on day five after surgery [9]. CCI is a validated score for postoperative morbidity, ranging from 0 (no complication) to 100 (death). This score is based on the Clavien-Dindo classification of postoperative complications, and it weighs the severity of the complications by the resources needed to treat them [10]. CCI offers a sensitive endpoint and is particularly suitable for randomised controlled trials [11].

Regarding secondary outcomes, our hypothesis is that our experimental strategy will reduce the quantity of fluid administered during surgery. Therefore, the secondary outcomes will be the total amount of fluid administered perioperatively and the lung ultrasound score (LUS). LUS is a simple, fast and reproducible measure to assess the potential harm of excessive fluid administration [12]. To assess long-term outcomes, the CCI will be measured at days 15 and 30.

### Participant timeline

Patients will be recruited during their pre-anaesthesia consultation. The protocol will be explained, and written consent obtained. On the day of surgery, the patients will be randomly allocated to either the control group or the experimental group. During surgery, haemodynamic, ventilatory and pharmacologic data will be collected. In the post-anaesthesia care unit (PACU), an arterial and a venous blood gas analysis and an LUS will be performed in patients after tracheal extubation.

The patients will be monitored daily during the 5 days following surgery. A phone call will be made on day 15 and on day 30 to collect information about potential postoperative complications. The duration of participation for each patient included in the study will be 30 days. Patients cannot be included in another study for 30 days after their randomisation.

### Sample size

A sample size calculation was made from published data [9, 11]. In order to show a 10% difference in CCI between groups on day five after surgery, with a 0.9 power and a 0.05 alpha risk, 100 patients were needed per group. Considering a potential 10% loss to follow-up, we included 220 patients (110 patients per group). We chose a 10% difference in CCI because this represents a clinically significant decrease in postoperative complications (one grade on the Clavien-Dindo classification).

### Recruitment

Patients will be recruited during the anaesthesia consultation by a senior anaesthesiologist once the protocol has been explained and their written consent obtained.

### Allocation

Randomisation will be performed with the block randomisation technique to reduce bias and achieve balance in patient allocation. Randomisation will be stratified by the treatment centre to reduce selection bias. Randomisation will be performed on surgery day by the attending anaesthesiologist with the nQuery Advisor software (v.7.0, Statsols, USA).

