### Data collection, management and analysis

All data will be collected in real-time by the clinical research team of the participating centres using a case report form. The variables to be collected are as follows:Demographics (age, gender, ASA score, height, weight, BMI).Comorbidities: Charlson comorbidities score and preoperative score to predict postoperative mortality (POSPOM).Surgical risk (ACS NSQIP surgical risk evaluation) and surgical procedure.Perioperative:◦ Haemodynamic (continuous): mean, systolic and diastolic blood pressure, heart rate, cardiac output, stroke volume, stroke volume variation and ScvO_2_ for the patients in the experimental group.◦ Respiratory (every 30 min): tidal volume, respiratory rate, FiO_2_, positive end-expiratory pressure (PEEP).◦ Neurologic (every 30 min): bispectral index (BIS), suppression ration (SR).At the end of surgery: total volume of fluids administered (crystalloids and blood products), type and total amount of anaesthesia drugs used, use of an epidural analgesic.In the PACU: arterial and venous blood gas analysis, LUS.Postoperative (daily): type and severity of postoperative complications until day 5 postoperative. CCI score calculation on day 5.At day 15 postoperative: collection of postoperative complications between day 5 and day 15 and CCI score calculation on day 15.At day 30 postoperative: collection of postoperative complications between day 15 and day 30 and CCI score calculation on day 30.

Data entry will be performed using REDCap software. Data analysis will be performed by a statistician from the clinical research team, using SPSS software (v 17.0, IBM, USA).

Table 1 shows the schedule of enrolment, intervention and assessment during the study period.

**Table 1 Tab1:** Schedule of enrolment, interventions and assessments

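### Randomisation is stratified by centre and risk scores are collected, but the only tests named for day-5 CCI are unadjusted: valid, somewhat conservative, and less precise than they could be

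*Protocol article*

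**What the plan says.** All references are to the protocol article.

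- Allocation: blocked randomisation. "Randomisation will be stratified by the treatment centre to reduce selection bias".
- Study setting: "Three French hospitals in which major surgery is performed", so there are three strata.
- Outcomes: "The primary outcome will be the Comprehensive Complication Index (CCI) on day five after surgery", a score from 0 to 100.
- Data collection, management and analysis: ASA class, the Charlson score and POSPOM are recorded, as is "Surgical risk (ACS NSQIP surgical risk evaluation) and surgical procedure". Table 1 places these items on the day of surgery in the allocation column, ahead of the intra-operative period.
- Statistical methods: for continuous outcomes, "We will use the *t*-test to assess differences between parametric continuous variables", or "the Mann–Whitney test for non-parametric variables". Chi-square and Fisher tests cover categorical data. The section contains no centre term, no stratified test and no covariate-adjusted model.

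**The concern.** Blocking within centre keeps the arms balanced on centre, so differences between hospitals largely drop out of the treatment contrast. A two-sample test does not use this: its standard error still contains the between-centre variation. If centre predicts CCI, the reported standard error exceeds the real variability of the estimate, the test rejects too seldom under the null, and some power is lost.

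The risk scores are a separate matter. They were not used in the randomisation, so omitting them creates no mismatch. But the trial enrols ASA classes 2 to 4 and both abdominal and thoracic surgery, so prognosis is likely to vary widely. A preoperative score aimed at postoperative outcome is a plausible predictor of a complication index. The data will be in hand, and the named tests make no use of them.

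What is at stake is precision, not validity.

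**Working it through.** **Inputs from the article:** 100 analysed patients per group, power 0.90 and alpha 0.05 (Sample size), two-sided testing (Statistical methods), 1:1 allocation (Trial design), three centres (Study setting).

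**Not in the article:** the SD of CCI, and the share of CCI variance (R²) explained by centre or by a risk score. R² is assumed and varied below.

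**Step 1: the plan's own figure.** By the normal approximation, n per group = 2 × (1.960 + 1.282)² × (SD/δ)². Setting n = 100 gives δ/SD = 3.242 × √(2/100) = 0.458. If the 10% difference means 10 CCI points, the implied SD is 21.8. With no SD printed, the figure of 100 can be matched but not verified. The power figures below use only the ratio 0.458, so they do not depend on how the 10% is read.

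**Step 2: centre alone.** With blocking within centre, the true standard error of the difference is about √(1−R²) times the one the unadjusted test uses. Hence:

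- true size = 2 × [1 − Φ(1.960/√(1−R²))]
- excess interval width = 1/√(1−R²) − 1
- unadjusted power = Φ((3.242 − 1.960)/√(1−R²))
- centre-adjusted power = Φ(3.242/√(1−R²) − 1.960)

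For R² = 10%, √0.90 = 0.9487. Then 1.960/0.9487 = 2.066, giving size 3.9%. The width ratio is 1/0.9487 = 1.054. Unadjusted power is Φ(1.351) = 0.912 and adjusted power is Φ(1.457) = 0.927.

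| Centre R² (assumed) | True size | Interval too wide by | Power, unadjusted | Power, centre-adjusted | Loss (points) |
|---|---|---|---|---|---|
| 0 | 5.0% | 0 | 0.900 | 0.900 | 0 |
| 5% | 4.4% | 2.6% | 0.906 | 0.914 | 0.8 |
| 10% | 3.9% | 5.4% | 0.912 | 0.927 | 1.6 |
| 20% | 2.8% | 11.8% | 0.924 | 0.952 | 2.8 |

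Losses are taken from unrounded values. Unadjusted power itself rises above 0.90 here, because stratifying on a prognostic centre already steadies the estimate. The proper comparison is therefore between the two power columns, not with 0.90.

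**Step 3: a baseline risk score.** It was not stratified on, so leaving it out keeps power at 0.900 when centre adds nothing. Adjusting for a score with R² of 10% or 20% gives Φ(3.242/√(1−R²) − 1.960) = 0.927 or 0.952. That is what 100/0.90 = 111 or 100/0.80 = 125 patients per group would give unadjusted. On the 10-point reading, the 95% interval half-width falls from 6.05 points to 5.74 or 5.41.

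**Step 4: simulation check.** The set-up was three centres, blocks of 4 (assumed), 200 analysed patients, normal outcomes and 6,000 runs per scenario. The Monte Carlo standard error is about 0.3 points at a 5% size (√(0.05 × 0.95/6000) = 0.0028) and 0.4 points at 0.90 power (√(0.9 × 0.1/6000) = 0.0039).

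| Centre R² / score R² | Size: unadjusted, centre, centre + score | Power: unadjusted, centre, centre + score |
|---|---|---|
| 0 / 0 | 4.8%, 4.8%, 4.7% | 0.899, 0.899, 0.898 |
| 5% / 10% | 4.5%, 5.1%, 5.1% | 0.904, 0.912, 0.940 |
| 5% / 20% | 4.5%, 5.0%, 4.9% | 0.903, 0.911, 0.957 |
| 10% / 20% | 4.1%, 4.9%, 5.0% | 0.906, 0.920, 0.970 |

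In the last row the unadjusted model's mean standard error was 3.08, against an actual SD of the estimate of 2.93. The simulation agrees with the formulas: ignoring centre costs little, most of the gain comes from the score, and with no prognostic value the three analyses coincide.

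**The case against.** The strongest reply is that this belongs to the analysis plan. Statistical methods lists tests by type of variable. It sets out no separate primary-outcome model and does not rule out adjustment. The article is condensed, the full protocol is available on request, and an analysis plan may add covariates. That stands in part: a reader might infer that the trial has ruled out adjustment, and the text does not say so. But the section does commit to named tests and offers no other method for a continuous outcome. The point is about a method that is stated, not one that is absent.

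Second, nothing here is invalid. A reader might infer that the mismatch inflates type I error or biases the estimate. It does neither; the test errs towards caution. Nor is chance imbalance in surgical risk an uncorrected flaw, since the unadjusted standard error already allows for it.

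Third, the two issues differ in weight. Carrying the stratification factor into the analysis is established practice, with a small effect here. Adjusting for a risk score is an efficiency choice, and collecting scores to describe the population does not oblige the trial to adjust for them. It would be wrong to credit the larger power gain to the mismatch with the randomisation.

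Fourth, the interval figures apply only on the t-test route. If CCI is judged non-normal, the Mann-Whitney test supplies no interval for a mean difference. Power is still lost in that case, but the sizes above were not computed for a rank test.

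The second, third and fourth replies stand, and they limit the point to one of precision.

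**Conclusion.** The point holds as an efficiency weakness in a stated method. Randomisation uses centre and the named tests do not, and recorded baseline risk goes unused.

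For an assumed centre R² of 5% to 20%, the nominal 5% test has a true size of about 4.4% down to 2.8%. T-test intervals are about 2.6% to 11.8% too wide, and ignoring centre costs about 0.8 to 2.8 points of power. A baseline score explaining an assumed further 10% to 20% would bring power from about 0.90 to roughly 0.93 to 0.95 (0.940 to 0.957 in simulation with centre also at 5%). At R² = 0 there is no gain.

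The direction is secure. The size is not, because the documents give neither the SD of CCI nor any R². The power figures also take at face value the article's claim of 0.90 power with 100 per group. A reader might infer that the trial is underpowered or its primary result unreliable on this account; the documents do not support that. The change is worth making because it is nearly free.

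**What to change.** Before unblinding, specify the primary analysis of day-5 CCI as a linear model on arm, with centre as a fixed factor and one named baseline risk score already collected (POSPOM, for example). Use robust standard errors because CCI may be skewed, and report the adjusted mean difference with its 95% confidence interval. Name the single score in advance, so that the choice cannot follow the results.

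Keep the unadjusted test as a sensitivity analysis. If a rank test is retained, use the van Elteren test stratified by centre. Include centre in the secondary analyses (CCI at days 15 and 30, fluid volume, lung ultrasound score). Adjusting those for the risk score is optional, since the documents give no ground for expecting it to predict fluid volume or the ultrasound score.

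The cost is a few lines in the analysis plan and matching wording in Statistical methods. No further data or patients are needed.
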